#### Follow up

After 8 weeks of intervention, all participants will enter an additional 4 weeks follow-up period. Participants will not receive any intervention during the follow-up period. Researchers will conduct a telephone follow-up or home visit in 4 weeks. The subjective feelings of the participants, PSQI, ISI, HAMD, and GSRS will be recorded.

#### Quality assurance

In order to ensure that patients in the ARQE group can practice the correct posture of ARQE by themselves at home, we will provide them with a video of the exercise method of ARQE recorded by a TCM doctor with 10 years of experience and a booklet with specific practice details. Participants will receive a “work practice record” and will be asked to fill it after each exercise.

### Outcome measures

To ensure the authenticity of the results, all questionnaires will be conducted by trained independent assessors. Regardless of whether the subjects complete the research project, we will collect the results of all participants. The study schedule (including enrollment, intervention, post-intervention, and follow-up period) is shown in Table 1.

#### Basic patient information

Basic information consists of the patient’s personal information and vital signs. Personal information includes age, gender, occupation, education level, and course of illness. Vital signs include body temperature, heart rate, respiratory rate, and blood pressure.

### Primary outcome

The primary outcome is the PSQI score. The PSQI will be assessed at week 0, week 4, week 8, and week 12. PSQI is composed of 19 sleep-related items and finally integrated into 7 dimensions: subjective sleep quality, time to fall asleep, sleep time, sleep efficiency, sleep disorder, hypnotic drugs, and daytime dysfunction. Each dimension is rated from 0 to 3 from mild and severe, with a total score of 21 points. A score more than 7 points to the presence of insomnia. The higher the total PSQI score is, the worse sleep quality [29].

### Secondary outcomes

Secondary outcomes include the Insomnia Severity Index (ISI), Gastrointestinal Symptom Scale (GSRS), Hamilton Depression Scale (HAMD), and rs-fMRI scan. ISI, GSRS, and HAMD will be assessed at week 0, week 4, week 8, and week 12. The rs-fMRI scan will be assessed at week 0 and week 8.

### Insomnia severity index (ISI)

ISI consists of 7 items to evaluate the degree of difficulty in falling asleep or maintaining asleep, that is, sleep satisfaction, daytime function, impaired attention due to sleep, the degree of pain of insomnia, and the degree of attention to insomnia, each of which is measured by five scales, with a total score ranged from 0 to 28 points, 0–7 points without insomnia, 8–14 points for mild insomnia, 15–21 points for moderate insomnia, and 22–28 points for severe insomnia [30].

### Gastrointestinal symptom scale (GSRS)

GSRS consists of 15 items, which are categorized into three groups, namely, gastric dysfunction, dyspepsia, and intestinal dysfunction. Each item is measure by seven scales, with a total score ranged from 0 to 105 points, used to evaluate the severity of gastrointestinal symptoms during the latest month. The higher the total score is, the more severe the symptoms are [31].

### Hamilton depression scale (HAMD)

HAMD is a scale used to assess depression. The version used in this study consists of 17 items, with a total score ranged from 0 to 53 points: 0–7 points without depression, 8–17 is mild depression, 17–24 is moderate depression, and > 24 is severe depression [32].

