### Inclusion criteria for patients with insomnia

Participants who meet all the following criteria can be enrolled: [1] meeting the diagnostic criteria of ICSD-3 criteria of insomnia [2]; ISI scale score between 8 to 21 [3]; 20 to 45 years old, male or female [4]; HAMD score less than or equal to 17 [5]; not having received any treatments for insomnia for the past month, including medication, and acupuncture [6]; normal result of blood routine [7]; right-handed; and [8] understanding the process of this study and agreeing to participate and sign the consent form.

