#### Secondary outcomes analysis

Secondary outcomes included clinical scale outcomes and neuroimage outcomes. Clinical scale outcomes will be undertaken by using a similar approach as the primary analysis.

The neuroimaging outcomes were statistically analyzed as follows: an independent *t* test will be used to compare the ALFF value and functional connection of the abdomen group, behavioral cognitive education group, and healthy control group. The two-sample *t* test will be used to compare the ALFF values between the two groups. Data of the two groups will be compared using paired *t* test before and after treatment. Select the largest peak coordinates of the different brain regions after ALFF analysis, save the clusters where the peak coordinates are located as a mask as the region of interest (ROI), and calculate the difference in functional connection between the ROI and the whole brain. The specific process is the seed area (ALFF difference brain area) is functionally connected with all voxels of the whole brain, which is the FC average image. After a correlation of values obtained from each voxel is subject to Fisher’s R-to-Z transformation, the data between groups will be subject to a two-sample *T* test and the data within the groups were subjected to paired *T* test and FWE correction. All the statistical analysis and processing will be completed independently by a research staff who has not participated in the treatment and scale evaluation throughout the entire process.

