Chronic insomnia is a typical mind-body illness, which not only affects sleep function but also causes many other symptoms, such as mental health and digestive function. This study will evaluate the ARQE from multiple perspectives [40]. The most important thing in the treatment of insomnia patients with ARQE is to relieve the symptoms of insomnia. Therefore, in this study, PSQI and ISI scales which are most commonly used to evaluate sleep quality are selected to evaluate sleep quality and clinical effects of ARQE before and after intervention. Patients with insomnia often have some psychological and emotional abnormalities, which affect daytime function and aggravate the patient's symptoms. Therefore, HAMD will be used to assess the patients’ psychological depression. As a treatment method to treat insomnia from the spleen and stomach, we will use GSRS to reflect the gastrointestinal function of insomnia patients. We will observe changes in the gastrointestinal function of patients with insomnia before and after treatment to verify whether ARQE relieves the symptoms of insomnia by improving the gastrointestinal function and further verify the theory the theory of “inharmonious stomach function leads to insomnia”.

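### The 17-item HAMD total may itself score insomnia, so a sleep difference can show up as a depression difference; add a score without the insomnia items and base mood statements on it

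*Protocol article*

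**What the plan says.** All references are to the protocol article.

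- **Instrument.** The section on the HAMD says: "The version used in this study consists of 17 items". It describes only a summed score and its severity bands, "with a total score ranged from 0 to 53 points: 0–7 points without depression" and upward. It does not list the items.
- **Role.** Under Secondary outcomes: "Secondary outcomes include the Insomnia Severity Index (ISI), Gastrointestinal Symptom Scale (GSRS), Hamilton Depression Scale (HAMD), and rs-fMRI scan". On timing: "ISI, GSRS, and HAMD will be assessed at week 0, week 4, week 8, and week 12".
- **Meaning.** The Discussion gives PSQI and ISI the task of measuring sleep. It then says: "Patients with insomnia often have some psychological and emotional abnormalities, which affect daytime function", and concludes that "HAMD will be used to assess the patients’ psychological depression".
- **Analysis.** Under Secondary outcomes analysis: "Clinical scale outcomes will be undertaken by using a similar approach as the primary analysis". The primary analysis section plans between-group tests, a repeated-measures ANOVA with a group-by-time term, and Bonferroni-corrected pairwise comparisons of time points for each group.
- **Population.** Participants must meet ICSD-3 criteria for insomnia and score 8 to 21 on the ISI. They must also have a "HAMD score less than or equal to 17". Major depressive disorder is an exclusion.

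The article does not mention overlap between the HAMD and sleep, and it describes no score or analysis that separates the two.

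**The concern.** The secondary outcomes are meant to cover different domains: sleep, gastrointestinal symptoms, depression and brain function. A difference on the depression scale will naturally be read as a result about mood. That reading fails if part of the depression score is itself a sleep score.

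This trial is exposed for three reasons. All participants have insomnia, so any sleep items are unlikely to be zero at entry. Depression is held low by the entry limit and the exclusion of major depressive disorder, so sleep items could make up a sizeable part of the total. Both treatments aim at sleep, so those items are expected to move.

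What is at stake is the interpretation of one secondary outcome. A HAMD difference between the arms, or a fall within an arm, could repeat the sleep result and be reported as a mood effect.

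**Working it through.** **Inputs from the protocol.** Planned PSQI difference 1.47; PSQI SDs 2.06 (ARQE) and 2.65 (CBTI); two-sided α 0.05; power 0.80; 51 per arm, or 57 after 10% loss; PSQI maximum 21 points from seven dimensions scored 0 to 3; HAMD range stated as 0 to 53; HAMD entry limit 17.

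**Assumptions not in the protocol.** The 17-item version has three insomnia items scored 0 to 2, so a block of at most 6 points. The SD of the HAMD total is 3 to 5. Mood does not differ between the arms.

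**Step 1: the plan's own figure.** n per arm = 2 × [SD × (1.960 + 0.842) / δ]². With SD 2.65 and δ 1.47 this gives 51.01, which matches the stated 51 (strict rounding up would give 52). Then 51 / 0.9 = 56.7, so 57. This calculation concerns PSQI only; no figure is stated for the HAMD.

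**Step 2: share of the score.** 6 / 53 = 11% of the stated range. Against the entry limit it is at most 6 / 17 = 35%. The second figure is an upper bound at baseline, not an expected share.

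**Step 3: shift implied by the planned sleep effect.** If the PSQI difference spreads evenly over its 21 points, the shift on a 6-point block is 1.47 / 21 × 6 = 0.42 HAMD points.

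**Step 4: chance of p < 0.05 with no mood difference.** The standard error is SD × √(2/57), which is 0.56, 0.75 and 0.94 for SD 3, 4 and 5. The ratio 0.42 / SE is 0.75, 0.56 and 0.45. Two-sample t test, 57 per arm:

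| Shift in HAMD total | SD 3 | SD 4 | SD 5 |
|---|---|---|---|
| 0.42 (scaled from the plan) | 12% | 9% | 7% |
| 0.5 | 14% | 10% | 8% |
| 1.0 | 42% | 26% | 19% |
| 1.5 | 75% | 51% | 36% |

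With 51 per arm the first row is 11%, 8% and 7%.

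**Step 5: uneven effect.** PSQI also scores hypnotic drugs and daytime dysfunction, which insomnia items would not mirror. As an illustration, if the whole 1.47 lay in three of the seven dimensions (9 points), the shift would be 1.47 / 9 × 6 = 0.98, close to the 1.0 row. That is an extreme case; the protocol does not say where the gain is expected.

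**Step 6: within-arm change.** Four time points give six pairwise comparisons, so α = 0.05 / 6. With 57 in an arm and an assumed SD of change of 3, 4 or 5, a fall of 1 point from the sleep items alone is significant with probability 42%, 21% or 12%. A fall of 2 points gives 99%, 85% or 61%. The falls of 1 and 2 points are assumptions.

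**The case against.** The strongest objection is that the premise is not in the article. It gives the number of items, a range and severity bands, but not the item content. This stands as a limit: the number and weight of insomnia items are assumptions about a named instrument, and every figure above depends on them. It does not remove the point, because the protocol fixes the instrument and the version, and the sponsor can check its own form in minutes.

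A second objection is that using a scale's full total as a secondary outcome is ordinary, and that extra scores may be left to an analysis plan. The first half is true, and it is why the total should stay. However, the article itself assigns the scale the meaning of psychological depression, and that reading is what the overlap weakens.

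Third, a reader might infer that the trial intends to claim an antidepressant benefit. The documents do not support that. The stated aims concern insomnia and brain function, and the Discussion introduces the HAMD because emotional problems accompany insomnia. The risk lies in how a difference would be read, not in an announced claim.

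Fourth, the larger percentages should not be taken as expected. Shifts of 1.0 and 1.5 points are about 2.4 and 3.6 times the 0.42 that follows from the planned effect. The planned handling of dropouts as unchanged from baseline would also dilute the shift somewhat.

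**Conclusion.** The point holds in a limited form. The 17-item total cannot by itself support a statement about mood in this trial, because a sleep difference can move it without any change in mood.

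At the planned sleep effect the between-arm distortion is modest: about 0.4 points, and a chance of p < 0.05 of about 7% to 12% instead of 5%. It is larger if the sleep gain is concentrated in falling and staying asleep, and larger for within-arm changes. These figures rest on three insomnia items scored 0 to 2, a HAMD SD of 3 to 5, and proportional scaling from PSQI.

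A reader might go further and infer that any sleep difference will appear as a depression difference. That is not supported. The assumed block is about 11% of the stated range and coarsely scored, so small sleep differences may not register at all. The primary PSQI conclusion, the sample size and eligibility are unaffected. The change is worth making, but the trial does not depend on it.

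**What to change.** 1. Confirm on the case report form which HAMD items score insomnia and how, and whether the scale is recorded item by item. The article does not state this.
2. Keep the 17-item total for the entry criterion and as the stated secondary outcome.
3. Add the HAMD score without its insomnia items, at the same visits and with the same analysis.
4. State in advance that any conclusion about mood, between or within arms, rests on that added score.

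If items are already recorded, this needs no new visit, data or patient burden. The costs are one extra analysis and a score to which the published severity bands do not apply, and which is harder to compare with HAMD totals elsewhere. Recruitment had already begun, and the protocol sends modifications to the ethics committee and the registry, so the addition should follow that route and be dated before the data are analysed.

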#### Neuroimaging

Fifteen participants of each group will receive rs-fMRI scan at weeks 0 and 8.

#### Rs-fMRI scan

The rs-fMRI data was collected by a 3.0 T Siemens MR scanner from Yueyang Hospital of Integrated Traditional Chinese and Western Medicine affiliated to Shanghai University of Traditional Chinese Medicine through a coil with a 32-channel head and neck coil. The sequence parameters of MRI are as follows: blood oxygen-dependent level fMRI (BLOD-fMRI), repetition time (TR) is 2000 ms, echo time (TE) is 30 mm, flip angle is 90°, and field of view (FOV) is 220 × 220 mm^2^; thickness/gap = 4.0/0.6 mm, and voxel size is 3 × 3 × 3. Participants should rest for half an hour before scanning and will be required to pay attention during the scanning process. All scanning operations are performed by relatively fixed radiation technicians and members of the research team during MRI operations. To ensure that the participants remain awake, the researchers will ask the subjects whether they are awake during and after the scan.

#### fMRI data preprocessing

Functional magnetic resonance data based on MATLAB 2013b (Math Works, Natick, MA, USA) platform pictures and picture parameter statistics software (http://www.fil.iom.ucl.ac.uk/spm, SPM12), static interest function Toolkit VBM8 (http://dbm.neuro.uni-jena.de/vbm8), and DPARSF V2.2 (http://rfinri.org/DPARSF ring state data processing assistant).

Data processing should be noted as follows: [1] removal of the data of the first ten points of time to ensure the stability of the signal, [2] slice timing correction: to eliminate the difference in fMRI signal interval scanning time, [3] head movement correction: to eliminate the artifacts generated by head motion and ensure the image quality, [4] spatial normalization to match the functional image with the structural image after head motion-correction to make it coincide with the standard brain, [5] reduction and elimination of noise generated in the previous step, [6] removal of the linear drift and exclusion the linear trend caused by the machine’s long time working temperature, and [7] filtering process to exclude high-frequency physiological noise and low-frequency drift.

### Composition of the coordinating center and trial steering committee

This project is directly supervised and managed by the research team of School of Acupuncture-Moxibustion and Tuina of Shanghai University of Traditional Chinese Medicine. The research team and special case inspectors from Yueyang Hospital of Integrated Traditional Chinese and Western Medicine affiliated to Shanghai University of Traditional Chinese Medicine set up a research steering group. The members of the Steering Group may conduct sampling checks on the completion of the case report form at any time.

### Composition of the data monitoring committee, its role, and reporting structure

The Data and Safety Monitoring Board (DSMB) will be composed of a physician, TCM doctor, medical statistician, ethicist, and radiologist and will oversee the study throughout the study period. The DSMB will supervise the safety data and clinical efficacy reports and monitor protocol compliance, data quality, and participant recruitment every month.

### Plans to promote participant retention and complete follow-up

To ensure retention of participants, they will be contacted by phone or WeChat 1 day before outcome assessment and will be reimbursed for round-trip travel. Participants have the right to withdraw at any stage of the study. When participants express a desire to withdraw from the study, the researchers will clarified any doubts and inform them of the potential benefits of being in the study. If a participant withdraws from the study, the researcher will try to contact the withdrawn participant to inquire about the reason for the withdrawal, whether there is an AE and outcome assessment.

### Safety assessments

If the participants experience any discomforts or unexpected situations during the clinical trial, they should inform the researchers immediately, regardless of the causes of these conditions. The researchers will do their best to prevent and treat any possible injuries caused by this study. Important AEs in this study would be qigong exercise-related AEs, such as headache, dizziness or vertigo, distension of head, tinnitus, stuffiness in the chest and worsening shortness of breath, heart-pounding or palpitations, muscular soreness or pain, profuse cold perspiration, irritability, neurasthenia, hallucination and paranoia, and psychological stress. Minor AEs will be treated immediately by the attending TCM doctor. In addition, all severe adverse events will be reported to the Regional Ethics Review Committee of Yueyang Hospital of Integrated Traditional Chinese and Western Medicine affiliated to Shanghai University of Traditional Chinese Medicine within 24 h. If adverse events are determined to be related to the study, the Regional Ethics Review Committee of Yueyang Hospital of Integrated Traditional Chinese and Western Medicine affiliated to Shanghai University of Traditional Chinese Medicine have the right to suspend this study. If an adverse event occurs during the clinical trial, medical experts will be recruited to evaluate and investigate the actual causes and medical and financial compensations will be made to the participant.

### Data management

Patients’ experimental data will be registered with electronic case report form separately by two researcher groups and verified by a third party. Any errors will be corrected and recorded immediately. All original data will be reserved for clinical data analysis and safety evaluation. All study-related data will be stored securely at the Shanghai University of Traditional Chinese Medicine.

### Statistical analysis

#### Primary outcome analysis

With previous set single blind rule, an independent statistician will analyze the clinical data by SPSS V.24.0 statistical software. Data analysis will be based on the intention-to-treat (ITT) principles. The results of ITT analysis will be compared for consistency. A *p* value < 0.05 will be considered statistically significant. Participants who fail to complete the study will be treated as having no change from baseline at all times in both groups. The Kolmogorov–Smirnov test will be used to test the normality. Appropriate transformations will be applied for non-normal distribution, The continuous variables with normal distribution will be described as mean and standard deviation, while continuous variables with non-normal distribution will be expressed by using median and interquartile interval (IQR), the categorical variable will be expressed in number and proportion.

To compare the baseline characteristics between two groups, Student’s *t* test or Mann–Whitney test will be used for continuous variables. Pearson’s *χ*-squared or Fisher’s exact will be used for categorical variables. To compare the primary and secondary outcomes between groups, continuous data will be tested by Student’s *t* test or non-parametric test. Pearson’s *χ*-squared or Fisher’s exact test will be applied for categorical data at baseline and after intervention. Repeated-measures ANOVA using the group-by-time interaction terms will be used to analyze the between-group differences. Multivariate analysis of variance will be used and the two-two comparisons among the changes in questionnaire scores with repeated measurement times for each group will be done by Bonferroni correction.

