#### Sample size calculation

The required sample size is calculated using an estimation formula based on the difference between two sample means and standard deviations (Pittsburgh Sleep Quality Index, which is assessed using composite points of sleep quality). A previous clinical study suggests that the mean and standard deviations of Pittsburgh Sleep Quality Index (PSQI) in ARQE group(*n* = 40) after treatment are 8.45 and 2.06, while the mean and standard deviations of PSQI in CBTI group (*n* = 40) after treatment are 9.92 and 2.65 [26, 27]. The sample size is calculated in the following formula, with the two-sided significance level (α) set at 0.05 and statistical power at 0.80 [28]. Thus, a minimum sample size of 51 participants per group (102 participants in total) is calculated to provide sufficient statistical power to detect a between-group mean difference of 1.47 in treatment efficiency, defined as the change in PSQI score.

Considering a 10% loss to follow-up, we aim to recruit 57 patients in each group, in a total of 114 patients. According to fMRI studies, 15 to 30 patients are adequate to test hypotheses.

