### Withdraw criteria

(1) The participant has an adverse event related to the research.

(2) At the participant’s own request.

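### Setting every non-completer to zero PSQI change at all visits discards observed scores, was not carried into the sample size, and can bias the comparison either way if loss differs by arm

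*Protocol article*

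**What the plan says.** Under Primary outcome analysis the article commits to intention-to-treat and then fixes the handling of non-completers: "Participants who fail to complete the study will be treated as having no change from baseline at all times in both groups". Nothing elsewhere limits this to visits without data. Secondary outcomes analysis extends a similar approach to the other clinical scales.

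PSQI is measured at weeks 0, 4, 8 and 12, and the abstract counts the four follow-up weeks as part of the 13-week study. Missing week 12 is therefore a failure to complete the study.

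Under Outcome measures the article says: "Regardless of whether the subjects complete the research project, we will collect the results of all participants". The retention section adds that withdrawn participants will be contacted where possible, outcome assessment included.

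The sample size section plans "with the two-sided significance level (α) set at 0.05 and statistical power at 0.80", on ARQE values that "after treatment are 8.45 and 2.06" and CBTI values that "after treatment are 9.92 and 2.65", in order "to detect a between-group mean difference of 1.47 in treatment efficiency, defined as the change in PSQI score". It arrives at 51 per arm and then says: "Considering a 10% loss to follow-up, we aim to recruit 57 patients in each group".

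**The concern.** There are three separate problems.

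1. **Observed data are overwritten.** A participant who completes all eight treatment weeks and misses only the follow-up visit has real week-4 and week-8 scores set back to baseline. The imputed zeros then enter the tests as if measured, with no allowance for uncertainty.
2. **The sample size rests on a different treatment of loss.** Going from 51 to 57 restores the number of completers. The analysis rule instead keeps non-completers in as zeros, which lowers the expected difference and adds variance between completers and non-completers.
3. **Unequal loss becomes a treatment difference.** If both arms improve, the arm that loses more people is pulled further toward zero. The result is bias whose direction depends on which arm loses more, so the rule cannot be defended as reliably conservative.

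At stake are the power of the primary comparison and, under unequal loss, its estimate and type I error.

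**Working it through.** **Inputs from the article:** post-treatment PSQI 8.45 (SD 2.06) for ARQE and 9.92 (SD 2.65) for CBTI; difference 1.47; two-sided alpha 0.05; power 0.80; 51 per arm; 10% loss; 57 per arm.

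**Assumptions, not in the article:** baseline PSQI B of 12 to 15; the post-treatment SDs stand in for the SD of change; completers have the planning means; the split of loss between arms.

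**Step 1. Reproduce the plan.** n = 2 × [SD × (1.960 + 0.842) / 1.47]². With SD 2.65 this is 51.01, matching the stated 51. With the pooled SD, √[(2.06² + 2.65²)/2] = 2.373, it is 40.9, which does not match. Inflation: 51 / 0.90 = 56.7, so 57. The plan's figures are reproduced with the larger SD in both arms.

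**Step 2. Equal loss p.** Completers improve on average by B − 8.45 (ARQE) or B − 9.92 (CBTI), and non-completers by 0. The expected difference is (1 − p) × 1.47, which at p = 0.10 is 0.90 × 1.47 = 1.323. The variance in each arm is (1 − p) × SD² + p(1 − p) × (mean improvement)².

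Example, B = 13 and SD 2.65 in both arms:
- ARQE: mean improvement 4.55; variance 0.9 × 7.0225 + 0.09 × 20.70 = 8.18
- CBTI: mean improvement 3.08; variance 0.9 × 7.0225 + 0.09 × 9.49 = 7.17
- Standard error √[(8.18 + 7.17)/57] = 0.519; ratio 1.323 / 0.519 = 2.55; noncentral-t power 71.5%

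Power at 57 per arm with 10% loss in both arms:

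| Assumed baseline PSQI | SD 2.65 in both arms | SD 2.06 and 2.65 |
|---|---|---|
| 12 | 74.9% | 82.6% |
| 13 | 71.5% | 78.9% |
| 14 | 67.3% | 74.2% |
| 15 | 62.6% | 68.8% |
| 51 completers per arm, full 1.47 | 79.2% | 87.2% |

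Even without the extra variance, restoring 80% at SD 2.65 needs 51.01 / 0.90² = 63 per arm.

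**Step 3. Unequal loss with a true difference of 1.47 (B = 13).**
- 15% ARQE, 5% CBTI: 0.85 × 4.55 − 0.95 × 3.08 = 3.868 − 2.926 = 0.94; power about 43% with SD 2.65.
- 5% ARQE, 15% CBTI: 0.95 × 4.55 − 0.85 × 3.08 = 4.323 − 2.618 = 1.70, above the true 1.47.

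Over B = 12 to 15 the first split gives 1.04 down to 0.74 and the second 1.60 up to 1.90.

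**Step 4. Unequal loss with no true difference.** If completers in both arms improve by c points, the false difference is (0.15 − 0.05) × c. For c = 3 to 6 that is 0.3 to 0.6 points. At c = 4 and SD 2.65 the variances are 8.01 and 7.43, the standard error is 0.520, and the test rejects about 12% of the time. Over c = 3 to 6 the rejection rate is about 9% to 18% instead of 5%. With equal loss the false difference is zero.

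**The case against.** The strongest defence is that counting non-completers as unimproved in both arms is a recognised, pre-specified failure rule. Under such an estimand a difference in loss is part of the effect, and the complaint about imputation uncertainty largely falls away. The article states no such estimand, so this tempers the bias argument without removing it. A planned power of 80% on the full 1.47 also does not fit such an estimand.

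The power shortfall depends on the SD. With the two stated SDs and baseline 12, power is still 82.6%, so it would be wrong to say that 80% is missed in every case. What remains under either SD is a loss relative to the same number of completers.

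The analysis plan is not shown, and the article speaks of comparing intention-to-treat results for consistency. It names no comparator, however, and an unseen sensitivity analysis would not change a stated primary rule.

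Some stronger readings are tempting but not supported:
- **That the rule always dilutes the effect below 1.47.** It does with equal loss, or with more loss in ARQE; enough extra loss in CBTI inflates it.
- **That non-completion will depend on arm.** One withdrawal criterion is "The participant has an adverse event related to the research", and the important adverse events listed are qigong-related. But the criterion covers both arms, no frequencies are given, and the Discussion plans equal therapist contact. Unequal loss is possible, not shown.
- **That the article contradicts itself.** Collecting everyone's results and then not using some of them is wasteful and in tension with the commitment, but the two statements can both be carried out. For withdrawn participants the article promises only an attempt at contact.

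**Conclusion.** The concern holds as a badly fixed rule, not as a missing detail. Overwriting observed scores follows from the wording alone and needs no assumption. The mismatch with the sample size is also certain: at the planned 10% loss in both arms the expected difference drops by 0.147 points, to 1.32.

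The power loss is moderate and conditional on the unstated baseline and SD of change: about 4 to 17 percentage points below 51 completers with SD 2.65 (79.2% to between 74.9% and 62.6%), and about 5 to 18 points with the two stated SDs (87.2% to between 82.6% and 68.8%).

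The bias under unequal loss is a demonstrated property of the rule, but its size here is illustrative. The 15%/5% split, baseline 13 and the 3 to 6 point improvement have no source in the article, and neither arm can be named in advance as the one favoured.

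**What to change.** Remove the no-change rule as the primary handling and state instead that:
- every observed PSQI score is kept and analysed in the randomised arm, including scores obtained after withdrawal;
- the primary analysis is a likelihood-based repeated-measures mixed model with arm, visit, arm-by-visit and baseline PSQI (or multiple imputation), with the arm contrast taken at the trial's primary visit. The article does not single out one visit, so that choice has to be stated separately;
- no-change imputation is kept only as a sensitivity analysis and fills only visits that are truly missing.

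Apply the same wording to the secondary clinical scales. If the sponsor does want non-completion to count as failure, the estimand should say so, observed scores before drop-out should still not be overwritten without a stated reason, and the sample size should be recalculated on the diluted difference.

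The cost is wording only, settled before unblinding: no extra participants or data, and SPSS can fit the mixed model. The small downside is that the primary model assumes data missing at random, which the sensitivity analysis probes.
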